This early-phase trial is designed to assess the safety, feasibility, and preliminary efficacy of RIC in slowing cognitive decline in patients with mild Alzheimer’s dementia. By evaluating the tolerability and safety of daily RIC over 3 months and its effects on plasma biomarkers and inflammatory factors, this study aims to lay the groundwork for future research on RIC as a potential intervention for AD-related cognitive decline.

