## Outcomes

### Outcomes for safety

The primary safety outcomes of this study are to evaluate the safety profile of RIC. Specifically, the following adverse events will be monitored:

1)  Psychological and Emotional Impact: Clinical observations and previous research have highlighted that patients with AD often experience feelings of helplessness and depression as their cognitive function declines and their ability to perform daily activities diminishes. These emotional challenges can lead to anxiety and fears about disease progression. Additionally, the pressure sensation caused by RIC training may exacerbate these feelings. To address this, the psychological condition of patients will be assessed using the HAMA and the HAMD-17, and the incidence of related adverse events will be calculated.2)  Procedure Tolerability: Instances of participants being unable to tolerate either the RIC or sham RIC procedures, resulting in suspension from the study, will be recorded as adverse events.3)  Physical Injuries: Signs of tissue or neurovascular injury potentially caused by RIC or sham RIC procedures will be monitored. This includes assessments such as palpation of the distal radial artery for pulsation, visual inspection for local edema, erythema, or skin damage, and palpation for tenderness in the affected areas.4)  Vital Sign Monitoring: Participants’ vital signs, including body temperature, respiratory rate, blood pressure, and heart rate, will be recorded to identify any potential systemic effects of the intervention.

All adverse events will be reviewed and independently determined by trained members of the research team who are blinded to the randomization group. These outcomes aim to comprehensively evaluate the safety of RIC and ensure that any risks associated with the intervention are carefully monitored and managed.

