In this study, participant safety is closely monitored through structured safety management protocols. If a participant experiences psychiatric worsening, indicated by significant increases in anxiety or depression scores (HAMA or HAMD-17), an immediate referral to a psychiatrist will be initiated, and psychiatric interventions or modifications to study procedures may be recommended as appropriate. In cases of physical injury, such as tissue damage, neurovascular compromise, or significant pain related to the cuff procedure, the intervention will be immediately paused. A multidisciplinary specialist team, including experts in neurology, cardiology, neurosurgery, and vascular surgery, will promptly evaluate the participant. Treatment will be provided as needed, and the participants will be closely monitored until full resolution. Detailed records of these events will be documented and reviewed by our Data and Safety Monitoring Board (DSMB) to ensure thorough oversight and appropriate follow-up actions.

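### The only tolerability outcome counts intolerance only when it leads to suspension from the study, so lesser intolerance goes uncounted and tolerability is liable to be overstated

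*Protocol article*

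**What the plan says.** The Introduction gives as an aim "evaluating the tolerability and safety of daily RIC over 3 months". Outcomes for safety opens with "The primary safety outcomes of this study are to evaluate the safety profile of RIC" and lists four items to be monitored.

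Item 2, procedure tolerability, is the only one about tolerating the cuff. It reads: "Instances of participants being unable to tolerate either the RIC or sham RIC procedures, resulting in suspension from the study, will be recorded as adverse" events.

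Item 3, physical injuries, sets no suspension condition. It includes "visual inspection for local edema, erythema, or skin damage, and palpation for tenderness in the affected areas".

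The safety-management paragraph in the same section describes a different course. It groups cuff-related pain with physical injury: for tissue damage, neurovascular problems "or significant pain related to the cuff procedure, the intervention will be immediately paused". The participant is then evaluated, treated as needed and followed to resolution, and the DSMB reviews the records.

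Adherence to RIC appears in Statistical analysis only as a predictor for imputing missing cognitive scores. It is not listed as an outcome.

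**The concern.** Item 2 joins two things: not tolerating the procedure, and being suspended from the study. The protocol itself foresees cuff problems that fall short of leaving the study, because it describes a pause. Yet its tolerability outcome has no place for them, and it does not say whether a suspension and a pause are the same thing.

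The intervention is a 45-minute session every day for 3 months, in people with mild dementia. Partial intolerance is a central question in such a schedule: sessions declined, sessions ended before the fifth cycle, or the cuff given up while clinic visits continue. A definition that registers only suspension would miss these cases in one of the four primary safety items. Followed exactly, it can only lower the count.

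**Working it through.** The plan gives no intolerance rate, threshold or power, and 20 per group is set by precedent (Sample size estimation). There is no plan figure to reproduce. The check is mainly a reading of the passages side by side.

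**Step 1: where each kind of event lands on the plain reading of item 2.**

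| Event | Tolerability outcome (item 2) | Recorded elsewhere? |
|---|---|---|
| Intolerance with suspension from the study | Counted | – |
| Pause for injury or significant cuff pain, then resumed | Not counted | Yes: documented and reviewed by the DSMB |
| Local signs or tenderness, no suspension | Not counted | Yes: item 3 |
| Session refused or stopped early for lesser discomfort | Not counted | No safety item names it; adherence data may reflect it |
| Cuff given up, participant stays in follow-up | Not counted, unless this is what suspension means | No safety item names it; adherence data may reflect it |

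The last two rows are the gap.

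**Step 2: the other reading.** The clause about suspension is set off by commas and could state a consequence: whoever cannot tolerate the procedure is suspended. Nothing would then go uncounted by definition. But stopping the cuff would be tied to leaving the study, which does not fit a paragraph in which a participant with significant cuff pain has only the intervention paused. The two paragraphs need reconciling on either reading.

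**Step 3: illustration of the plain reading. Both rates are assumptions.** Let p be the true proportion with intolerance of any degree and s the share of those who are suspended. The counted rate is q = p × s. With 20 per arm, the expected count is 20q and the chance of counting none is (1 − q)^20.

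| p | s | q | Expected count | P(none counted) |
|---|---|---|---|---|
| 10% | 1 | 10% | 2.0 | 0.122 |
| 10% | 1/2 | 5% | 1.0 | 0.358 |
| 10% | 1/4 | 2.5% | 0.5 | 0.603 |
| 20% | 1 | 20% | 4.0 | 0.012 |
| 20% | 1/2 | 10% | 2.0 | 0.122 |
| 20% | 1/4 | 5% | 1.0 | 0.358 |
| 30% | 1 | 30% | 6.0 | 0.001 |
| 30% | 1/2 | 15% | 3.0 | 0.039 |
| 30% | 1/4 | 7.5% | 1.5 | 0.21 |

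For example, with p = 20% and s = 1/4, q = 0.05 and 0.95^20 = 0.358.

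An arm with 0 of 20 counted has an exact two-sided 95% upper limit of 1 − 0.025^(1/20) = 16.8%. In the 20% rows, a zero count would therefore give an interval that excludes the true rate. That happens with probability 0.012 if all intolerance is counted, and 0.12 to 0.36 if only a half or a quarter is.

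**The case against.** The strongest case against is that much of what matters is recorded anyway, and it largely stands for the more serious events. The safety-management paragraph treats significant cuff pain as physical injury and has such cases documented for the DSMB. Item 3 takes in tenderness and local signs without any suspension. Sessions take place at staffed stations, and adherence is evidently collected, since it serves as an imputation predictor.

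A reader might therefore infer too much from item 2, and three stronger readings fail:

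- *Paused sessions and pain are not recorded.* They are, for injury and significant pain. What is true is that they do not enter the tolerability outcome.
- *The daily sessions yield no tolerability data unless someone leaves.* Adherence, injury and vital-sign data contradict this.
- *Tolerability decides whether Phase II goes ahead.* No go/no-go rule is stated. Sample size estimation links confidence in Phase II to the number of patients.

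It is also fair to say that suspension is undefined and might cover a temporary halt, and that session-log detail commonly sits in the full protocol. The first point is itself a reason to define the term. The second does not remove the concern, because the article does not leave the event open: it states the definition for a primary safety item. DSMB records are also not a between-arm tolerability outcome, and no safety item names sessions refused or shortened for lesser discomfort.

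**Conclusion.** The concern holds in a limited form. On the plain reading of item 2, intolerance below significant pain or injury, and stopping the cuff while staying in follow-up, are left out of the only tolerability outcome. Tolerability is liable to be overstated, and the documents do not allow the amount to be estimated. The figures above show direction and plausible scale only, under assumed values of p and s.

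Two further consequences are tempting but not established. An under-count concentrated in the RIC arm, narrowing the difference from sham, would follow if discomfort below the threshold is more frequent at 200 than at 60 mmHg. That is plausible, but the documents give no data on it. Loss of the 6- and 12-month assessments would follow only if suspension means leaving the study, which is undefined. The restriction of the analysis to completers is a separate matter, though it could also remove suspended participants from the analysed set.

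**What to change.** Change how events are counted:

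1. Reconcile item 2 with the safety-management paragraph by defining suspension and pause, and by separating both from leaving the study.
2. Define the tolerability outcome, by arm and in all randomised participants who started a session, as the number with at least one session refused, shortened or paused because of intolerance.
3. Report permanent stops of the procedure on their own line, apart from leaving the study, together with the proportion of scheduled sessions completed.
4. State that participants who stop the procedure stay in the planned 3-, 6- and 12-month assessments.

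Nothing here sets a rule on when to pause or stop treatment. The cost is a change of wording and one line in the session log, which staff at the stations could complete. The downside is a possibly less favourable tolerability figure.

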To evaluate the long-term efficacy of RIC, the study includes a 12-month follow-up period with assessments at 6 and 12 months. These evaluations include neurocognitive scales and blood biomarkers analyses. The RIC intervention itself is administered over a 3-month period, with data collection points at baseline, 3 months, 6 months, and 12 months to systematically assess its sustained effects (Figure 2).

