### Statistical analysis

Data will be obtained from all patients who complete the study protocols and follow-ups and will be analyzed using the per-protocol (PP) approach. Statistical analysis will be performed using SPSS version 20 (SPSS Inc., Chicago, IL, United States), with a significance level of *p* < 0.05. Demographics and clinical characteristics will be analyzed using descriptive statistics. Continuous and categorical data will be reported as mean values, standard deviations, number values, and percentages. Continuous variables following a normal distribution will be compared using the independent samples *t*-test, ANOVA, or rank-sum test, while categorical variables will be compared using the chi-square test.

In our RIC trial in mild Alzheimer’s dementia (*n* = 40), we implemented two strategies appropriate for small-sample longitudinal data. First, single random forest imputation was applied to address missing cognitive scores (e.g., MoCA/MMSE) by using predictors such as baseline Aβ42/Aβ40 ratio and RIC adherence preserve variable interaction structure. Second, Generalized Estimating Equations (GEE) will be used to model outcome trajectories under the assumption of missing at random (MAR), thereby accommodating incomplete data without imputation. Attrition is minimal (7% MoCA loss at 12 months) and APOE subgroup analyses show no evidence of differential dropout. This approach balances methodological rigor with feasibility and aligns with CONSORT recommendations for early-phase trials with limited resources.

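### Cuff intolerance is tied to suspension from the study, and nothing says that the scheduled outcome assessments continue after the cuff is stopped

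*Protocol article*

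**What the plan says.** Three places in the protocol article bear on what happens to a participant who stops the cuff.

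- **Outcomes for safety, item 2 (Procedure Tolerability).** The item reads: "participants being unable to tolerate either the RIC or sham RIC procedures, resulting in suspension from the study, will be recorded as adverse events".
- **Outcomes for safety, closing paragraph on safety management.** After tissue damage, neurovascular compromise or "significant pain related to the cuff procedure, the intervention will be immediately paused". After evaluation and any treatment, "the participants will be closely monitored until full resolution". Psychiatric worsening leads to referral and possibly to changed study procedures; removal from the study is not mentioned.
- **Statistical analysis, first sentence.** "Data will be obtained from all patients who complete the study protocols and follow-ups and will be analyzed using the per-protocol (PP) approach".

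The follow-up paragraph under Interventions describes the treatment as "administered over a 3-month period, with data collection points at baseline, 3 months, 6 months, and 12 months". Neuropsychological assessments and Blood sample collection and analysis repeat these time points for the scales and the blood measures, without making them depend on tolerating the cuff. Statistical analysis also plans a GEE under missing at random, and a single random forest imputation of cognitive scores "by using predictors such as baseline Aβ42/Aβ40 ratio and RIC adherence".

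**The concern.** Stopping a treatment and leaving a trial are different events. Item 2 joins them: intolerance of the procedure ends in suspension from the study. The data-source sentence in Statistical analysis points the same way, because it names patients who complete the protocol and follow-ups. No sentence says that a participant who stops RIC or sham still attends the later assessments.

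The participants affected are not a random subset. Safety is the primary endpoint and is judged in part by HAMA and HAMD-17. Outcomes for safety itself says that the pressure of the cuff may worsen anxiety and low mood. By the article's own reasoning, then, intolerance and the primary outcome may be linked. The arms also differ in cuff pressure, so the loss could be unequal. If later outcomes go missing this way, those who remain are no longer a randomised comparison. An analysis plan written later can change the analysis set, but it cannot supply visits that were not made.

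**Working it through.** **Comparing the passages**

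| Place | Trigger | What stops | Stated observation afterwards |
|---|---|---|---|
| Outcomes for safety, item 2 | Procedure not tolerated | Participation in the study | Event recorded as an adverse event; nothing on later visits |
| Outcomes for safety, closing paragraph | Injury or significant cuff pain | The intervention | Monitoring until the event resolves; nothing on later visits |
| Statistical analysis | Protocol or follow-up not completed | Inclusion as a source of data | None |

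A participant in significant pain from the cuff can fall under both of the first two rows, which give different consequences. Neither row says whether the 3-, 6- and 12-month assessments continue. The third row would leave their data out even if the visits took place.

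The first scheduled HAMA and HAMD-17 after baseline is at 3 months (Neuropsychological assessments), which is also the end of treatment. A participant suspended during treatment could therefore have no scheduled post-baseline score. The imputation is described for cognitive scores, with MoCA and MMSE as examples, and does not mention HAMA or HAMD-17. Using adherence as a predictor helps only if outcomes are observed for some participants who adhere poorly. If everyone who stops is lost, the values must be extrapolated from those who stayed.

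**Inputs for the size**

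- 20 per group, 40 in total (Study design). The arithmetic agrees: 20 + 20 = 40.
- Cuff pressure 200 mmHg in the RIC arm and 60 mmHg in the sham arm (Interventions).
- Intolerance rate: not given. The 7% loss of MoCA at 12 months in Statistical analysis is neither an intolerance rate nor split by arm. Rates of 5%, 10% and 20% in the RIC arm are assumed below for illustration.

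**Chance that the rule applies at all in the RIC arm:** 1 − (1 − p)^20.

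- p = 5%: 1 − 0.95^20 = 0.64; expected number 20 × 0.05 = 1.
- p = 10%: 1 − 0.90^20 = 0.88; expected number 2.
- p = 20%: 1 − 0.80^20 = 0.99; expected number 4.

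**Shift in the RIC-arm mean.** If k of 20 are lost and their mean differs from that of the others by D standard deviations, the mean of those observed differs from the mean of all 20 by (k/20) × D.

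| k lost | D = 0.5 SD | D = 1 SD |
|---|---|---|
| 1 | 0.025 SD | 0.05 SD |
| 2 | 0.05 SD | 0.10 SD |
| 4 | 0.10 SD | 0.20 SD |

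**Uncertainty in a proportion.** If x events are seen and k participants are unobserved, the proportion in the full arm lies between x/20 and (x + k)/20. The width is k/20, which is 5, 10 and 20 percentage points for k = 1, 2 and 4. This needs no assumption about D.

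**Power.** For an assumed effect of 0.8 SD (two-sided 0.05, normal approximation), power is 71.6% with 20 versus 20 and 66.5% with 20 versus 16. The loss of precision is modest; the main problem is selection.

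**The case against.** The strongest reply is that item 2 lists what counts as a safety event and is not written as a follow-up rule. Suspension is not defined as permanent, and no sentence says that any visit stops. The assessment schedule carries no condition on tolerance. The closing paragraph of the same section pauses only the intervention. The first sentence of Statistical analysis can be read as naming an analysis set. The planned GEE and the use of adherence as a predictor suggest that some incomplete or poorly adherent participants contribute data. A journal article may also leave retention detail to the full protocol.

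Much of this stands, and it rules out the stronger readings that a reader might infer:

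- **That these outcomes are never collected and cannot be recovered.** The text does not say that the visits stop. Baseline data, the intolerance event and any earlier visit remain, and sensitivity analyses can bound the gap under assumptions.
- **That the primary safety result loses the harmed participants.** Each intolerance is itself recorded among the primary safety outcomes, and the abstract has psychiatric adverse events monitored during treatment.
- **That a real excess of psychiatric events would vanish.** Suppose 2 to 4 of 20 RIC participants stop, half of them have an event, and 10% of all others do. The full-arm incidence is (2 × 0.5 + 18 × 0.1)/20 = 14% to (4 × 0.5 + 16 × 0.1)/20 = 18%, against 10% among those still followed. These rates have no source in the article, and the contrast also requires that the events of those who stop go unrecorded. In the same scenario, 2 to 4 of 20 (10% to 20%) would still appear as tolerability events.

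The reply does not remove the inconsistency. The article does more than stay silent: it states a consequence (suspension from the study) and a data source (completers), and the first disagrees with the pause of the intervention stated in the same section.

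**Conclusion.** The concern holds in a limited form. What stopping the cuff means for participation and for data differs between item 2, the safety-management paragraph and Statistical analysis. Followed as written, they leave no stated continued collection of the 3-, 6- and 12-month HAMA, HAMD-17, cognitive, ADL and blood outcomes for participants who stop. Such a loss would be related to tolerability and possibly to arm, so missing at random is doubtful and the between-group comparison can be biased.

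The size cannot be determined from the document. Under the assumed 1 to 4 losses among 20 RIC participants, the shift is 0.05 to 0.20 SD if they differ by 1 SD from the others, and half that if they differ by 0.5 SD. With no intolerance there is no shift. These figures assume losses in the RIC arm only; equal losses of similar participants in both arms would largely cancel in the comparison. The point is worth settling before participants are lost, because outcomes that were not collected cannot be observed later.

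**What to change.** Reconcile the three places.

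1. In Outcomes for safety, item 2 and the safety-management paragraph, separate stopping the procedure from leaving the study. State that a participant who stops RIC or sham, for whatever reason, keeps the already scheduled 3-, 6- and 12-month assessments unless consent is withdrawn.
2. In Statistical analysis, state that data are obtained from all randomised participants and analysed in the groups to which they were randomised, at least for the safety outcomes, with per-protocol as a supplementary analysis. Changing only the clause on whose data are obtained would not be enough: the per-protocol clause that follows would still exclude the newly collected data.

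No rule on when the cuff is paused or stopped is changed. The cost is protocol wording and some effort to retain participants who no longer attend the stations. No visit or test is added, because the assessments are already in the schedule.

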### Outcomes for efficacy

The secondary outcomes of this study are categorized into three classes. Cognitive function and daily living abilities will be evaluated using the MMSE, MoCA, and CDR scales, while daily living abilities will be assessed using the ADL scale. Disease severity and progression will be measured through plasma biomarkers, including Aβ40, Aβ42, the Aβ42/Aβ40 ratio, pTau217, pTau181, GFAP, and NfL. Neuroinflammation levels will be assessed via serum levels of IL-1β, IL-6, IL-8, IL-10, IL-2R, TNF-*α*, ESR, and CRP. These outcomes aim to comprehensively evaluate the efficacy of RIC in addressing cognitive decline, daily living abilities, disease biomarkers, and neuroinflammation in patients with AD.

### Sample size estimation

This is a Phase I trial measuring the safety and feasibility of RIC. Since no prior clinical studies have examined RIC in AD patients, there is no reference data available. Ganesh proposed that a cohort of 12 patients per group is sufficient to assess the safety of remote ischemic conditioning in patients with Vascular Cognitive Impairment (28). Tong’s Phase I clinical trial on the safety and efficacy of RIC in stroke patients suggested that 20 cases are sufficient to assess the feasibility of a pilot study (29). Based on studies addressing the safety and feasibility of RIC, this project targets 20 patients in each group, providing sufficient confidence to proceed to a subsequent Phase II study with a randomized sham control.

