## Abstract

**Objective:**

Alzheimer’s disease (AD) is characterized by complex pathological mechanisms involving neuroinflammation, oxidative stress, and vascular dysfunction. Remote Ischemic Conditioning (RIC) has shown potential in addressing these pathways by improving cerebral blood flow, reducing oxidative stress, and modulating inflammatory responses. This protocol focuses on evaluating the safety, feasibility, and preliminary efficacy of RIC as a multi-target intervention for delaying cognitive decline in patients with mild Alzheimer’s dementia, aiming to improve cognitive outcomes and overall quality of life.

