**Methods and expected results:**

This study is a randomized, controlled, single-center, prospective clinical trial designed to evaluate the safety, feasibility, and preliminary efficacy of RIC in patients with mild Alzheimer’s dementia. Eligible participants will be recruited and randomly assigned to either the RIC group or a control group receiving sham RIC, with 20 patients in each group. Participants will receive either RIC or sham RIC once daily over a 3-month period. Outcome measures will assess cognitive function, psychological well-being, and inflammatory and neurodegenerative biomarkers. Psychiatric adverse events will be monitored throughout the treatment using the Hamilton Anxiety Rating Scale (HAMA) and the Hamilton Depression Rating Scale (HAMD-17). Cognitive function and daily living abilities will be evaluated at baseline, 3 months, 6 months, and 12 months post-treatment using the Mini-Mental State Examination (MMSE), Montreal Cognitive Assessment (MoCA), Clinical Dementia Rating (CDR), and the Activities of Daily Living (ADL) scales. In addition, blood samples will be collected at each time point to measure plasma biomarkers of *β*-amyloid species and serum inflammatory cytokines to assess potential changes in cognitive decline, disease progression, and inflammation. The primary endpoint is safety, with the expectation that RIC will not increase psychiatric adverse events as reflected in HAMA and HAMD-17 scores. Primary efficacy endpoints include improvements in MMSE, MoCA, CDR, and ADL scores, indicating potential cognitive benefits and enhanced daily functioning. Secondary endpoints will analyze biomarkers to evaluate disease progression and inflammation levels before and after treatment.

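### Feasibility is a headline objective and part of the sample-size reason, but no outcome is assigned to it, and the completers-only sentence, read literally, removes the participants who would inform it

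*Protocol article*

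**What the plan says.** All references are to the protocol article.

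- **Objective.** The Abstract describes the protocol as "evaluating the safety, feasibility, and preliminary efficacy of RIC" and the trial as "designed to evaluate the safety, feasibility, and preliminary efficacy of RIC in patients with mild Alzheimer’s dementia". The Abstract's conclusion repeats the aim, and the Introduction has "This early-phase trial is designed to assess the safety, feasibility, and preliminary efficacy of RIC".
- **Sample size.** Sample size estimation says "This is a Phase I trial measuring the safety and feasibility of RIC". It cites two precedents: for safety, that "a cohort of 12 patients per group is sufficient to assess the safety of remote ischemic conditioning", and for feasibility, a stroke trial that "suggested that 20 cases are sufficient to assess the feasibility of a pilot study". It then sets 20 per group and says this is enough to justify going on to Phase II.
- **Outcomes.** There are two headings, safety and efficacy. Under efficacy: "The secondary outcomes of this study are categorized into three classes". These are cognition and daily living, disease biomarkers, and neuroinflammation. Under safety, the procedure-tolerability item counts participants in either arm who are suspended because they cannot tolerate the procedure, and classes them as adverse events.
- **Analysis.** Statistical analysis opens with "Data will be obtained from all patients who complete the study protocols and follow-ups" and specifies a per-protocol approach. Its second paragraph describes a trial of 40, single imputation of missing cognitive scores with RIC adherence among the predictors, GEE under missing at random, and a 7% loss of MoCA at 12 months.

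**The concern.** A stated objective needs at least one quantity that answers it. The article lists every scale, cytokine and biomarker, and none of its listed outcomes is assigned to feasibility. Recruitment, sessions delivered, completion of the course and retention do not appear as outcomes.

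The question is not idle. Under Interventions, participants with dementia attend a community station every day for 3 months, and the sample-size section says no earlier clinical study of RIC in AD exists to draw on. The trial could therefore be reported as having shown feasibility, and used to support Phase II, without an estimate of whether participants received or completed the treatment. The completers-only sentence adds to this, because those who stop are the ones who carry the information about feasibility and tolerability.

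**Working it through.** **1. The plan's own figure.** 2 × 20 = 40, which agrees with the stated total. Nothing else in the sample size can be reproduced: the article gives no effect, event rate, precision target, power or dropout allowance. The target equals the feasibility precedent (20) and exceeds the safety precedent (12 per group).

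**2. Objective against outcomes.**

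| Aim | Outcome assigned |
|---|---|
| Safety | Four items under Outcomes for safety |
| Preliminary efficacy | Three classes under Outcomes for efficacy |
| Feasibility | None; intolerance suspensions are counted under safety |

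Adherence is named as a predictor in an imputation model. It is not summarised as a result.

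**3. What the completers-only sentence does if read literally.** Let r be the number randomised in an arm and c the number who complete.

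- Completion among randomised = c/r.
- Completion in the completers set = c/c = 100% for any c above 0.
- Intolerance suspensions: k/r among randomised, and 0/(r − k) = 0% among the rest, assuming a suspended participant does not later return and complete.

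**4. Illustrations.** The article gives no expected completion, so the counts are assumed. Exact (Clopper-Pearson) 95% limits for x of n: lower = the 0.025 quantile of Beta(x, n − x + 1); upper = the 0.975 quantile of Beta(x + 1, n − x).

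| Assumed result | Among randomised (exact 95% CI) | Completers set |
|---|---|---|
| 18 of 20 in one arm complete | 90% (68.3 to 98.8) | 18/18 = 100% |
| 16 of 20 in one arm complete | 80% (56.3 to 94.3) | 16/16 = 100% |
| 36 of 40 overall complete | 90% (76.3 to 97.2) | 36/36 = 100% |
| 32 of 40 overall complete | 80% (64.4 to 90.9) | 32/32 = 100% |
| 1 of 20 suspended for intolerance | 5% (0.1 to 24.9) | 0/19 = 0% |
| 2 of 20 suspended for intolerance | 10% (1.2 to 31.7) | 0/18 = 0% |
| 4 of 20 suspended for intolerance | 20% (5.7 to 43.7) | 0/16 = 0% |

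**5. The second paragraph of Statistical analysis.** Imputation, GEE for incomplete data and a non-zero loss figure all require participants who did not complete. They cannot coexist with a data set restricted to completers, so the section contradicts itself. Resolving the conflict in favour of the second paragraph does not fill the gap. Its methods apply to cognitive scores and outcome trajectories. Its 7% concerns one scale at one visit, and 7% of 40 is 0.07 × 40 = 2.8, not a whole number of participants (2/40 = 5%, 3/40 = 7.5%).

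**The case against.** The strongest reply has four parts.

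*Tolerability already measures feasibility.* In part it does: intolerance leading to suspension is a form of discontinuation and is recorded in both arms. A reader might infer that the trial records nothing bearing on feasibility; the safety section rules that out. But missed sessions, withdrawal for other reasons and loss to follow-up are not covered by that item.

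*The analysis set does not fix the completion rate.* A reader might infer that the trial is bound to report 100% completion. The article does not support that. The result follows from one sentence, which the next paragraph contradicts, and nothing says completion would be calculated within the per-protocol set. It could be counted from enrolment records. This stands, and it limits the 100% and 0% figures to the literal reading of that sentence. The missing outcome does not depend on the reading.

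*A condensed article leaves such things to the full protocol or SAP.* Metric definitions and interval methods may well be left there. Here, though, the article itself lists its outcomes under two headings and states its analysis set, and neither matches the objective it repeats. That the sentence about three classes sits under an efficacy heading is fair, but there is no third heading for feasibility.

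*The illustrations show imprecision, not bias.* The intervals do show only what 20 per arm can deliver, and they would remain after the fix. The contrast between the two denominators is what shows the problem.

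Two further inferences should also be resisted. The article does not say that daily attendance is the main doubt about RIC. Nor does it say that attendance is logged session by session; its use of adherence as a predictor implies only that some adherence measure is held.

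**Conclusion.** The point holds in this form: feasibility is a stated objective and part of the reason for 20 per group, and no outcome is assigned to it. Only intolerance leading to suspension is recorded, as a safety event, and adherence serves only as an imputation predictor. As written, the plan cannot answer one of its own questions, and its claim about readiness for Phase II has no feasibility estimate behind it.

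The effect of the completers-only sentence is conditional. Read literally, it turns any completion rate into 100% and any intolerance suspension rate into 0%; with 16 of 20 completing, that is 100% in place of 80%. It also conflicts with the paragraph after it, and the two need to be reconciled. The counts are assumed for illustration. No arithmetic error in the sample size is claimed. This should be corrected, but it does not by itself undermine the efficacy comparisons.

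**What to change.** 1. Add a feasibility outcome class, analysed on all randomised participants and shown by arm: sessions delivered as a proportion of those scheduled (from the adherence data the plan already relies on), proportion completing the 3-month course, and retention at 12 months.
2. Give exact 95% confidence intervals for the participant-level proportions. Summarise session delivery per participant first, because sessions within one person are not independent.
3. Analyse tolerability suspensions on the same all-randomised denominator.
4. Reconcile the completers-only sentence with the imputation and GEE paragraph, and state that it does not govern feasibility or tolerability.
5. Have the sponsor state before unblinding what level of these measures would support going on to Phase II, or drop that claim.

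The cost is protocol wording and one short table, with no extra participants. If adherence is not yet held per session, a simple attendance record is also needed. The drawback is width: at 20 per arm even 18 of 20 gives 68% to 99%, and the report would have to show that.
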